### Community Health Centres

As a result of extensive consultation with both the Beijing Health Bureau and Fengtai Health Bureau, it has been agreed that all CHCs located in the Fengtai district will participate in the study, that is, 22 CHCs will be involved in the implementation of the study. An information session will be conducted for all CHC staff, which will thoroughly explain the administrative and implementation aspects of the study. In addition, a member of the research team will visit each CHC to meet with staff and answer specific questions in relation to the study.

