### Sample size

Based on conventional methods for estimating a sufficient sample size in a randomised trial with two conditions, and assuming that individuals are randomised to conditions, the number of participants needed is determined mainly by three parameters [27]. These parameters are: (1) the tolerable Type I error rate (assuming the null hypothesis); (2) the desired level of statistical power (assuming the alternative hypothesis); and (3) an anticipated effect size for a relevant test statistic (e.g., standardised mean difference). Consistent with general conventions, [27] the current study specified a 5% Type I error rate as tolerable and required 80% power. The primary outcome measure was glycosylated haemoglobin (HbA1c), measured on a continuous scale, and a recent meta-analysis evaluating psychological interventions to improve glycaemic control in patients with T2DM [21] indicates an expected standardised effect of 0.32 across studies. This was the anticipated effect size estimate specified in the current investigation. Based on these parameters, and using the G*Power 3.1 program [28] to conduct calculations, it was ascertained that a sample size of *n *= 306 (153 per group) would be sufficient to detect an effect size of 0.32 with 80% power, while maintaining 5% Type I error.

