As noted, the sample size calculations reported above assume that individuals are randomised to groups. In contrast, cluster randomisation, as used in the current study, is associated with less statistical power; especially when individuals within clusters are similar [29]. This degree of similarity is quantified by the Intra-Class Correlation (ICC) coefficient, which can then be used, along with estimates of the average cluster size (in terms of number of participants per cluster) [30] to calculate an adjusted sample size; inflated to yield the same level of statistical power as if individual randomisation was used [29]. Only a limited number of clusters were available to the current study, and estimates were calculated assuming this fixed number (*k *= 22). As described by Campbell et al. (2000), ICCs for outcome variables in primary care research are generally lower than 0.05, and this value was also specified in the adjusted calculations. A sample size calculator for cluster-randomised trials is available [29] and was used to estimate the required sample size given cluster randomisation. Allowing for a participant attrition rate of 20%, it was estimated a total sample of *n *= 1320 would be required to achieve at least 80% power, while maintaining 5% Type I error. This figure reflects 60 patients per CHC (cluster), and 660 per intervention group.

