Analyses will consider participant trajectories over time, and evaluate whether these differ according to levels of exposure to the intervention. Through multilevel analysis, variation in outcome scores will be partitioned across three levels, including: (1) variation in repeated measures within participants, modelled as a function of the initial level (intercept), linear trajectory, and Level-1 residual that may be autocorrelated and heteroscedastic (although different models of the Level-1 error covariance structure can be evaluated [53]); (2) inter-individual variation in the intercept and trajectory, specified as a function of the cluster mean and Level-2 residual assumed to be independently and normally distributed; and (3) variation in cluster means for both intercept and trajectory. The between-cluster variation in trajectory, specifically, is then modelled as a function of an intercept, Level-3 covariate (reflecting exposure to the intervention), and residual. The test statistic for the parameter reflecting experimental condition is used to test the null hypothesis of no treatment effect [54]. One-sided tests will be used in all instances, and a level of p < 0.05 will be used to evaluate statistical significance of the primary outcome. Secondary analysis will use the critical level of p < 0.001 to control Type I error probabilities due to testing across multiple outcomes.

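### The primary HbA1c test is one-sided at 5% without a stated reason, although the sample size reproduces only for a two-sided 5% test

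*Protocol article*

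**What the plan says.** The Statistical analysis section of the protocol article fixes the direction and level of testing: "One-sided tests will be used in all instances, and a level of p < 0.05 will be used to evaluate statistical significance". The sentence goes on to limit the 0.05 level to the primary outcome, which is HbA1c. For the other outcomes, "Secondary analysis will use the critical level of p < 0.001 to control Type I error probabilities due to testing across multiple outcomes". The one-sided rule covers both groups of tests. The null hypothesis is given as no treatment effect. The direction of the alternative is not written there; the Trial objective section implies it, since it speaks of improving HbA1c and the other profiles relative to usual care.

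The Sample size section says that "the current study specified a 5% Type I error rate as tolerable and required 80% power". It takes its effect size from a meta-analysis that "indicates an expected standardised effect of 0.32 across studies" and concludes that "306 (153 per group) would be sufficient to detect an effect size of 0.32 with 80% power, while maintaining 5% Type I error". It never says whether the 5% is one-sided or two-sided. The result is then inflated for 22 clusters, an intra-class correlation of 0.05 and 20% attrition, to 1320 participants (60 per CHC).

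**The concern.** A one-sided 5% test and a two-sided 5% test are different standards of evidence for a claim of benefit. If the trial was sized on the two-sided standard and is judged on the one-sided one, the bar for success is lower than the one the sample was calculated to clear.

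Three things are at stake:

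- The false-positive rate for the headline claim on HbA1c.
- How a borderline HbA1c result would be reported.
- Whether the plan can formally recognise worsening. It collects outcomes that could move either way under coaching, such as weight, blood pressure, psychosocial distress and quality of life, and it nowhere argues that worsening is impossible or of no interest.

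**Working it through.** **Inputs.** From the Sample size section: standardised effect d = 0.32, 5% Type I error, 80% power, two equal groups, 22 clusters, ICC 0.05, 20% attrition, 60 enrolled per CHC. From the Statistical analysis section: one-sided tests, 0.05 for HbA1c, 0.001 for secondary outcomes.

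**Step 1: reproduce the stated 153 per group.** Formula: n per group = 2(z_α + z_β)² / d², with z_β = 0.842 and d² = 0.1024.

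| Test | z_α | n per group, normal | n per group, exact t | Power with 153 per group, exact t |
|---|---|---|---|---|
| Two-sided 5% | 1.960 | 2 × 2.802² / 0.1024 = 153.3 | 155 | 79.7% |
| One-sided 5% | 1.645 | 2 × 2.487² / 0.1024 = 120.8 | 122 | 87.4% |

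The two-sided calculation gives the stated 153. The one-sided calculation falls about 31 to 32 per group short of it, or 242 to 244 in total against 306.

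**Step 2: see whether the clustered total points the same way.** For a fixed number of clusters k, the number analysed per cluster is m = N(1 − ICC) / (k − N × ICC).

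- N = 306: m = 306 × 0.95 / (22 − 15.3) = 43.4, so 44 analysed. 44 / 0.8 = 55 enrolled per CHC, and 55 × 22 = 1210.
- N = 242: m = 242 × 0.95 / (22 − 12.1) = 23.2, so 24 analysed. 24 / 0.8 = 30 enrolled per CHC, and 30 × 22 = 660.

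A second route uses the design effect at 48 retained per CHC (60 less 20%), 1 + 47 × 0.05 = 3.35. It gives 306 × 3.35 / 0.8 = 1281 on the two-sided basis and 242 × 3.35 / 0.8 = 1013 on the one-sided basis. Neither route returns exactly 1320, but on both the two-sided figure is the nearer.

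**Step 3: chance of falsely claiming benefit on HbA1c.** With no true effect, the one-sided 5% test rejects in favour of coaching with probability 0.05 (critical z 1.645). A two-sided 5% test does so with probability 0.05 / 2 = 0.025 (critical z 1.960). The ratio is 2. A favourable result between these critical values has a two-sided p between 0.05 and 0.10. It would be significant under the plan and not under the two-sided test.

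**Step 4: secondary outcomes.** One-sided p < 0.001 corresponds to two-sided p < 0.002, which is stricter than a conventional two-sided 0.05. What the one-sided rule removes here is the ability to declare worsening significant.

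**Step 5: power of the enrolled trial under each test.** With 11 CHCs per group and 48 retained in each, the effective number per group is 11 × 48 / 3.35 = 157.6. The noncentrality is 0.32 × √(157.6 / 2) = 2.841.

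| Reference distribution | Two-sided 5% | One-sided 5% |
|---|---|---|
| Normal | 81.1% | 88.4% |
| t with 20 df (22 clusters − 2; an assumption, not stated in the protocol) | 77.1% | 86.4% |

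**The case against.** The strongest reply is that nothing in the protocol is formally contradictory. The Sample size section promises a 5% Type I error, and a one-sided 0.05 test has exactly that. The words 'two-sided' do not appear, so the mismatch is a back-calculation. The direction follows from an objective set in advance, and a trial sized generously and then tested one-sided is over-powered for its stated test, not under-powered. All of this stands. It does not explain why 153 per group was needed when about 121 to 122 would have served, and it supplies no reason for one-sided testing.

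Some stronger readings are tempting, and the protocol does not support them:

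- A reader might infer that every test is run at one-sided 0.05. The 0.05 level applies to HbA1c only, so the point about two-sided p between 0.05 and 0.10 does not extend to the secondary outcomes.
- A reader might infer that harm would go unseen. It could not be called statistically significant, but the planned summaries of mean change and the signed model estimates would show it.
- A reader might take 1320 as exact proof of two-sided sizing. Reaching it by the design-effect route takes a cluster size of 50 (306 × 3.45 / 0.8 = 1319.6), which the protocol does not give. The 48 implied by its own figures gives 1281. The clustered total is supporting evidence only; the inference rests on the 153 per group.

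**Conclusion.** The point holds as an unexplained mismatch between the sizing and the primary test. The chance of falsely claiming benefit on HbA1c is 5%, against 2.5% in the favourable tail of the two-sided 5% test that the sample size reproduces. 'Doubled' is meant only in that comparison; the nominal error rate of the planned test is 5%, as stated. On every outcome, worsening can be described but not declared significant.

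This rests on two inferences: that the sizing was two-sided, because only that calculation gives 153 per group, and that the one-sided alternative is improvement, as the objective implies. The gain in power from the one-sided rule is about 7 percentage points by normal approximation (88.4% − 81.1%), or about 9 with the assumed 20-df t reference (86.4% − 77.1%). It matters because it could decide whether the trial reports success on its primary outcome.

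**What to change.** Replace the sentence on one-sided testing with: *All tests are two-sided; the primary outcome is significant at two-sided p < 0.05, reported with a 95% confidence interval.* If a one-sided primary test is kept, set its level at 0.025. Make the secondary tests two-sided at their stated p < 0.001. State in the Sample size section that the 5% is two-sided. Make the change before outcomes are compared by arm.

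The cost is wording, plus lower power than the one-sided test gives. By normal approximation, with 48 retained per CHC and ICC 0.05, two-sided power is about 81%, so the stated 80% is still met without more recruitment. If the analysis will use a t reference with 20 degrees of freedom for the 22 clusters, two-sided power is about 77%, and the power stated in the protocol should be restated accordingly.

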### Qualitative study

Two qualitative studies will be conducted in parallel with the cluster RCT:

1. Participant experience: Focus groups will be undertaken with participants in each arm of the RCT. Purposive sampling techniques will be utilised to ensure a range of selected participants are recruited into the study. We will ensure that the sample includes men and women, age representation, and participants who represent a range of self-management behaviours and self-management skills and confidence levels. The focus group schedule will explore participants' attitudes and experiences of the health coach intervention.

2. Health coach experience: Focus groups will be undertaken with health coaches from each CHC. The focus group schedule will explore the barriers and enablers to the delivery of the intervention and the impact the intervention has had on their professional role. In addition, all health coaches will be completing diaries throughout the intervention. After each coaching session they will record their observation about the session including goals set by the patient and their own reflections on the coaching process. These diaries will be included in the analysis of the qualitative study to evaluate the process of the implementation of the intervention.

Data from the focus groups will be audio-taped, transcribed verbatim, translated into English and entered into NVIVO software [55] to organise the data. To increase rigour, each transcript will be independently coded line by line by two researchers. An inductive process of thematic analysis, as described by Braun and Clarke [56], will be employed to identify key issues and themes within the data.

## Discussion

This cluster RCT has been specifically tailored to the Chinese health care system and has the ability to make a large contribution to the evidence base for the management of patients with T2DM. It is hypothesised that the health coaching intervention delivered in this study will enhance the ability of patients to self-manage T2DM, leading to improved clinical and psychosocial outcomes, thus delaying diabetic complications. In addition, the components of metabolic syndrome and the risk factors for cardiovascular disease will be assessed.

To our knowledge, this is the first trial that combines both telephone and face-to-face health coaching in relation to T2DM management in China. Similar studies have been conducted in other countries, however these have primarily been telephone [57,58] or group based interventions [59,60]. Furthermore, this study will uniquely assess the benefits of intervention delivery for three time periods (6, 12 and 18 months), providing evidence for which is the optimal period of intervention.

This trial is being conducted in a real-world community health setting in China. By implementing the study in community health settings, this study empowers and builds capacity within the existing workforce. This approach embeds the study within community health settings, thereby increasing the generalisability of results [61].

The success of this study is reliant not only on the capacity of the participants to engage in behaviour change but also on the performance of individual health coaches. According to the spirit of MI, the therapeutic relationship is more like a partnership or companionship than expert/recipient roles [18]. It is therefore essential that health coaches are supported in their role. Several approaches have been incorporated into the intervention strategy to ensure coaches receive adequate support: following initial MI training, regular meetings will be scheduled with health coach coordinators; diaries will be kept by each health coach; and a peer support system will be implemented.

An additional challenge for this study will be to ensure that the back-translation of data collected remains an accurate representation of the original version. The use of two, independent, bilingual translators will increase the chances that the original meaning has been retained, will ensure literal accuracy and will help to detect mistakes [62].

This trial, with a strong focus on self-management and health coach support has the potential to be adapted to other chronic diseases, as well as other regions of China. The combination of both quantitative and qualitative methods utilised in this study will allow for a more comprehensive understanding of the implementation process [63], and will provide additional information to guide further research.

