## Methods

### Trial design

The current study is an evaluation of the Happy Life Club™, through an 18-month cluster randomised controlled trial (RCT). Cluster randomised sampling of community health stations was chosen to minimise experimental contamination between the control and intervention participants [25]. The Happy Life Club™ trial is managed jointly by Monash University - Melbourne, Peking University - Beijing and Fengtai Health Bureau - Beijing. The study protocol was approved by Monash University Human Research Ethics Committee.

CHCs will be randomly allocated to one of two groups:

1. Intervention group where patients with T2DM receive 18 months of health coaching in combination with usual care.

2. Control group where patients with T2DM receive 18 months of usual care only.

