### Outcome assessment

The trial will run for 18 months and outcome measurements will be assessed at baseline, and again at 6, 12 and 18 months by means of a clinical health check and a self-administered questionnaire. Anthropometric, and blood pressure measurements as well as fasting blood samples, will be taken by independent doctors and nurses from Peking University, who are blinded to group allocation. All participants will be instructed to fast overnight prior to each clinical health check for a minimum of eight hours. Blood samples will be analysed centrally at the CHC Laboratory blinded to group allocation.

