In the first two months participants will receive two face-to-face and four telephone coaching sessions per month. The frequency of the sessions will decrease over the 18 month intervention period as shown in Figure 2 such that in the last six months of the intervention, participants will receive one face-to-face session per month and one telephone session per three months. This reflects the philosophy of the MI approach whereby over time coach input diminished as the participants gain confidence in self-management. While there is no preset time frame for each health coaching session, it is anticipated from the pilot study that the duration of each telephone session will be approximately 20 minutes, and the face-to-face session approximately 30 minutes. Coaches will record the length of each session.

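### The Discussion promises evidence on the best length of coaching, but every intervention centre delivers the same 18-month tapered programme

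*Protocol article*

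**What the plan says.** Protocol article, Discussion: the authors contrast their study with earlier telephone or group-based interventions. They add that it will assess the benefit of delivering the intervention over three periods, in the words "6, 12 and 18 months), providing evidence for which is the optimal period of intervention".

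The Methods describe something narrower:

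- **Trial design:** "CHCs will be randomly allocated to one of two groups". The first is "Intervention group where patients with T2DM receive 18 months of health coaching in combination with usual care"; the second is "Control group where patients with T2DM receive 18 months of usual care only".
- **Intervention group:** one schedule for all coached participants. "In the first two months participants will receive two face-to-face and four telephone coaching sessions per month". Then "The frequency of the sessions will decrease over the 18 month intervention period", so that in the last six months "participants will receive one face-to-face session per month and one telephone session per three months".
- **Outcome assessment:** "outcome measurements will be assessed at baseline, and again at 6, 12 and 18 months". Here the three times are measurement points, the same in both arms.
- **Trial objective:** effectiveness against usual care at those three times. Length of coaching is not mentioned.

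**The concern.** The Discussion treats 6, 12 and 18 months as alternative lengths of intervention. The Methods treat them as visits within a single programme. To say which period is best, one has to compare programmes of different length at a common horizon, and the design contains only one length.

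What is at stake is the interpretation of the results. If the arm difference were largest at month 6, or flat from month 6 onwards, a reader who relied on the Discussion could conclude that six months of coaching is enough. The trial would hold no data on people who had six months of coaching and then none. A published protocol that announces evidence on duration in advance makes that conclusion look planned.

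**Working it through.** **1. What the sample size covers.** Inputs from Sample size: standardised effect 0.32, 5% type I error, 80% power, 22 CHCs, intra-class correlation 0.05, 60 patients per CHC, 20% attrition.

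- Individual randomisation, two-sided: n per arm = 2(1.96 + 0.8416)² / 0.32² = 153.3. The plan states 153 per group (306); rounding up gives 154 (308).
- Clusters per arm: 660 / 60 = 11. Retained per CHC: 60 × 0.8 = 48. Design effect: 1 + (48 − 1) × 0.05 = 3.35. Effective n per arm: 11 × 48 / 3.35 = 157.6. Two-sided power by the normal approximation: 0.81.

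The plan's figures are therefore reproduced on this approximation, and they refer to one contrast, coaching versus usual care. No contrast between lengths of coaching enters them.

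**2. What the visits estimate.** Write Y(t, s) for the mean outcome at month t when coaching runs until month s, with s = 0 for usual care. Coaching after month t cannot affect the outcome at month t (assuming no anticipation), so the arm differences are:

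| Visit | Estimated contrast |
|---|---|
| 6 months | Y(6, 6) − Y(6, 0) |
| 12 months | Y(12, 12) − Y(12, 0) |
| 18 months | Y(18, 18) − Y(18, 0) |

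Each is a randomised comparison and a valid estimate of the effect of the programme to date.

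**3. What a choice of period needs.** At a common horizon of 18 months one must compare Y(18, 6), Y(18, 12) and Y(18, 18). Only the last is observed. The other two require people whose coaching ended at 6 or 12 months, and the design has no such group.

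**4. Illustration (assumed values).** Suppose the standardised arm difference were 0.32 at all three visits. If the gain persists after coaching stops, six months would have given 0.32 at month 18. If the gain is lost once coaching stops, six months would have given 0 at month 18. The trial data are identical in the two cases, so they cannot tell them apart.

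**5. Length is tied to intensity.** In the first two months: 2 + 4 = 6 sessions per month. In the last six months: 1 + 1/3 = 1.33 per month. The ratio is 6 / 1.33 = 4.5. A plateau or decline in the arm difference after month 6 could come from longer coaching adding little, from thinner contact, or from time since coaching began. With one schedule for everyone these cannot be separated. The intermediate steps are in Figure 2, which was not available, but the text gives a single schedule for the whole intervention arm.

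**6. Whether the analysis could supply the contrast.** The Statistical analysis section mentions levels of exposure. Exposure enters there as a cluster-level covariate whose parameter reflects experimental condition, so it does not encode length of coaching. A comparison by sessions actually attended would be observational, and none is described. An analysis plan could add visit-specific contrasts, but these would still be the three in step 2.

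**The case against.** The strongest defence is that the sentence claims only to provide evidence, and the visits do provide some. If there were no difference at 6 months and a clear one at 18, that would bear on whether six months had been long enough to produce benefit. This stands: the trial describes how benefit builds up under its schedule. It does not reach the question of the best period, which depends on what happens after stopping.

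Four stronger readings are tempting, and the document does not support them:

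- *That the trial has a stated aim it cannot meet.* The Trial objective concerns effectiveness against usual care at three times and is sound. The disputed clause is an interpretive claim in the Discussion.
- *That the visit results are uninformative about time.* Each arm difference is a valid randomised estimate of the effect so far (step 2).
- *That calendar time is confounded with coaching.* Controls are assessed at the same visits, so trends common to both arms cancel. What remains entangled is coaching length, session frequency and time since the start of coaching.
- *That the single test on a linear trajectory leaves the time points uncompared.* The article also plans descriptive summaries of mean change over time. Visit-specific estimates may properly sit in the statistical analysis plan, which was not available.

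It is also fair to say that the taper is part of the programme as designed. That makes each estimate the effect of that programme to date; it does not make it the effect of a shorter programme.

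**Conclusion.** The claim about the best period is wrong as written. The design has two randomised groups and one planned length of coaching, so outcomes after stopping at 6 or 12 months are never observed, and neither a larger sample nor a fuller analysis plan would supply them. The arm differences at the three visits remain valid for what the objective asks.

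The point is minor. It concerns one clause of the Discussion; the objective, primary test, type I error and sample size are unaffected. The harm arises only if a conclusion about duration is later drawn from the results. The verdict rests on the text giving one schedule to all intervention participants, and on reading the best period as a comparison of programme lengths.

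**What to change.** Replace the clause in the Discussion with wording such as: *The trial describes the effect of one 18-month tapered coaching programme, compared with usual care, at 6, 12 and 18 months; it does not compare programmes of different length.*

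In the analysis and report, give the arm difference at each visit with its confidence interval, present these as the time course of the effect, and draw no conclusion about the best duration.

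The cost is a change of wording. Randomisation, coaching schedule, visits, primary test and sample size stay as they are.
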